### Interim analyses {21b}

N/A—no interim analyses are planned as part of this trial.

### Methods for additional analyses (e.g. subgroup analyses) {20b}

Secondary analysis will use a theory-based approach to explore the interplay of mechanisms and context [10], including model fidelity. This will involve adjusting for pre-specified baseline school and child level covariates to investigate the impact of the intervention arm for individual clusters. Multiple regression will be used with the number of intervention components as a predictor variable. In addition, %FSM and IMD will be used in a linear model as predictor variables. The study will have low power to detect all but the largest differences in subgroups.

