### Objectives {7}

The main aim is to assess the impact of the PhunkyFoods healthy lifestyle intervention programme, (developed and refined by Purely Nutrition), on food literacy, cooking skills and fruit and vegetable intake of children using usual practice in primary schools as the comparator. Intervention effects will be examined at 12 months. The cost-effectiveness of the intervention will be assessed from a societal perspective. In addition, differences in outcomes will be explored by model fidelity in each school setting, other healthy living initiatives in the local area and socioeconomic status using percentage eligibility for free school meals (%FSM) and the index of multiple deprivation (IMD) as covariables.

The PhunkyFoods programme is a flexible menu of options for schools to select from, making this a highly complex intervention. Following the Medical Research Council guidance on the evaluation of complex interventions, research perspectives will focus on effectiveness and theory-based approaches: the overall objective of the study is to explore to what extent the intervention produces the intended outcomes in real-world settings and what works in which circumstances [10].

The research hypotheses are as follows:The PhunkyFoods intervention group will show higher food literacy and cooking skills than the control group measured by mean scores.The PhunkyFoods intervention group will show a higher intake of fruit and vegetables than the control group measured by mean scores.Schools in the intervention arm that choose more ‘active ingredients’ (intervention components) from the flexible menu of options will have better outcomes than those schools that choose less ‘active ingredients’.The covariates, %FSM and IMD, will have a mediating impact on the outcomes for schools in the intervention arm.

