#### Criteria for discontinuing or modifying allocated interventions {11b}

Participating schools in the intervention arm will be given the freedom to choose from the flexible menu of active ingredients in the programme and work at the pace that is right for the individual school setting. In line with the PhunkyFoods Logic Model (Additional file 1), schools will be encouraged to participate in active ingredients 1 and 2 within the first 3 months as part of the model fidelity. Whilst the programme pace is led by schools, the EDCs will support and encourage participating schools to consider active ingredient 3 by 6 months of the programme and will highlight opportunities to select ‘Active Ingredients’ 4–8 after 6 months. This flexibility is indicative of the complexity of the trial and hence the theory-based approach to research perspectives and hypotheses which aim to understand the interplay of mechanisms and context in evaluating complex interventions [10].

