#### Strategies to improve adherence to interventions {11c}

The PhunkyFoods programme is run by Purely Nutrition. All EDCs are employed by Purely Nutrition and supported with training and guidance on how to implement the programme according to the Programme Manual [13] and the Logic Model, whilst providing the flexibility for schools to work at the pace that is right for their setting. The study will collect data on of how many components each school delivers and this will be included as part of the analysis.

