#### Sample size {14}

The study by Dean and colleagues in 2019, based on 469 participants and using CooC11 to assess cooking competence, showed a significant increase (*p* < 0.01) in cooking competence at follow-up after the camp-based intervention compared with results at baseline [15]. The results of CooC11 at baseline (mean (SD)) were 21.75 (7.89) and at follow-up 26.13 (8.89). The difference in cooking competence scores was therefore approximately 5 units, the equivalent of a moderate effect size (Cohen’s *d* = 0.52).

A power calculation was undertaken using STATA based on this moderate effect size of the Dean study. To detect this effect size with a minimum of 90% power and using a 2-level model with individuals clustered within schools (individual schools are being recruited rather than individual children), 13 clusters are needed in each arm. This calculation was based on the assumption that a mean of 15 children would be included in each school, and therefore, 195 children would be needed in each arm. The power is reduced when a large proportion of variation is at the school level (most of the variation will be at the individual level); in other words, children within a school may be more similar to each other than children at another school and therefore a conservative estimate of 20% of variation at the school level was assumed. It is likely that it is less than this, but there is too little information available related to cooking competence to be able to estimate it with more certainty. Due to the reasonable possibility that schools may drop out of the study, we aim to recruit 14 schools per arm (28 schools in total).

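### The third hypothesis rests on a component count that schools choose for themselves; the plan does not call it a non-randomised association and names no school term for its test

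*Protocol article*

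**What the plan says.** Objectives {7} lists as its third research hypothesis: "Schools in the intervention arm that choose more ‘active ingredients’ (intervention components) from the flexible menu of options will have better outcomes" than schools that choose fewer. It is directional and concerns differences among intervention schools.

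The count is not assigned. Under Criteria for discontinuing or modifying allocated interventions {11b}, intervention schools "will be given the freedom to choose from the flexible menu of active ingredients in the programme" and set their own pace. Strategies to improve adherence {11c} says the study will record "how many components each school delivers and this will be included as part of the analysis", which is one number per school.

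For the test, Methods for additional analyses {20b} says "Multiple regression will be used with the number of intervention components as a predictor variable". The same paragraph speaks of "adjusting for pre-specified baseline school and child level covariates", uses free school meal eligibility (%FSM) and deprivation (IMD) as predictors, and concedes low power for subgroups. The comparator section {6b} says current food teaching will be recorded and may be added as a further independent variable if that is judged suitable.

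The only multilevel statement is in Sample size {14}, which uses a two-level model of children within schools. Statistical methods {20a}, Methods for additional analyses {20b} and the Discussion name no school effect, cluster term or robust variance.

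**The concern.** There are two separate problems.

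The first is interpretation. Schools that take up more components may be the more motivated or better resourced ones, or may already teach food skills well. Any of these could raise scores whatever the programme does. Randomisation balances such factors between arms, but not between high-uptake and low-uptake schools within one arm. The article's caveats concern power (the additional-analyses section and the Discussion) and multiple testing ({20a}). None concerns self-selection. Nor is low power a safeguard, because confounding shifts the estimate itself.

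The second is precision. A predictor with one value per school carries the information of about 14 schools. A regression on individual children without a school term would take the residual degrees of freedom from about 210 children and give a standard error that is too small.

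At stake is whether a positive slope could be read as evidence that delivering more components produces better outcomes.

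**Working it through.** **Inputs.** Sample size {14} gives 14 schools per arm, a mean of 15 children per school, and 20% of variation at school level. It calls the 20% conservative and probably too high, so I also use ICC 0.05 and 0.10, which are my assumptions. The relevant ICC is the one left after covariate adjustment, a further reason to show a range.

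**The plan's own figures.** 14 × 15 = 210 children per arm and 13 × 15 = 195, as stated. The step to 13 schools does not reproduce. With d = 0.52, 90% power and two-sided 5% (the level is assumed, as none is given), 77.7 × 3.8 / 15 = 19.7, so 20 schools per arm. That is a separate sample-size matter and nothing below depends on it.

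**Error rate if children are analysed at a single level.** For a predictor constant within schools, the variance is understated by the design effect DE = 1 + (15 − 1) × ICC. The actual two-sided error is 2 × [1 − Φ(z / √DE)], with z = 1.96 for nominal 5% and 2.576 for nominal 1%.

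| ICC | DE | √DE | Actual error at nominal 5% | Actual error at nominal 1% |
|---|---|---|---|---|
| 0.05 | 1.7 | 1.30 | 0.133 | 0.048 |
| 0.10 | 2.4 | 1.55 | 0.206 | 0.096 |
| 0.20 | 3.8 | 1.95 | 0.315 | 0.186 |

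At ICC 0.20, 210 / 3.8 ≈ 55, so the 210 children carry the information of about 55 independent ones. The 1% level that {20a} says will be considered does not repair this.

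A simulation of 10,000 trials per setting (14 schools of 15, true component effect zero, count unrelated to the school) gave single-level rejection rates at nominal 5% of 0.132, 0.207 and 0.318 for the three ICCs. Regression on the 14 school means gave 0.051, 0.049 and 0.047.

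**What the school-level analysis leaves untouched.** The same simulation was run with the count correlated ρ with the underlying school effect, the true component effect still zero. The values of ρ are assumptions. Rejection rates at nominal 5%, ICC 0.20:

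| ρ | School-level model | Single-level model |
|---|---|---|
| 0.3 | 15% | 50% |
| 0.5 | 36% | 72% |
| 0.7 | 69% | 91% |

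At ICC 0.05 the school-level rates are 10%, 21% and 39%. Correct degrees of freedom therefore do not make the slope a programme effect.

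**Information available.** By Fisher's z, 80% power with 14 schools needs (1.96 + 0.84) / √(14 − 3) = 0.845, a school-level correlation of about 0.69. This agrees with the article's own concession of low power.

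**The case against.** The strongest reply concerns the unit of analysis. A reader might infer that the trial will treat 210 children as independent. The article does not say so. The hypothesis is worded about schools, the count is recorded per school, and a regression on 14 rows would fit the text. The Discussion calls this regression complex without defining it, and a full protocol exists that is not shown. This stands: the error rates above are conditional. What remains is that the section names multiple regression with child-level covariates and does not carry forward the two-level model used to size the trial.

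Second, some confounders are already planned for: baseline covariates, %FSM, IMD and, possibly, existing food teaching. That stands in part. No measure of staff motivation or capacity is named, and food teaching enters only at discretion.

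Third, a reader might infer that the investigators will claim a dose-response effect. The documents do not support that. They speak of exploring, promise cautious interpretation and hope only for some discussion. But the caution is tied to multiple testing, and the listed hypothesis says that schools choosing more components "will have better outcomes than those schools that choose less" components.

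Fourth, the aim "to investigate the impact of the intervention arm for individual clusters" might be read as a plan for school-specific effects, which a parallel design could not separate from each school's own level. The paragraph describes covariate-adjusted regression and specifies no such estimates, so I do not press a loose phrase.

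**Conclusion.** The concern holds in a limited form. It is firm that a listed, directional hypothesis is tested on a count that schools choose after allocation, and that the article never says the comparison is non-randomised. It is conditional that the test is anti-conservative: an actual error of about 13% to 31% at nominal 5% requires a single-level analysis of children, 15 per school, with ICC between 0.05 and 0.20. The top of that range uses the article's own ICC, which it expects to be too high. The size of the confounding cannot be known from the documents, and the simulated rates only illustrate it under assumed correlations. The randomised comparison of arms is not affected by this point. The matter is moderate: it concerns a secondary analysis, but one that answers a stated hypothesis.

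**What to change.** In Methods for additional analyses {20b}:

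- Fit the component-count model within the intervention arm, either on school-level data or with a school random intercept and between-school degrees of freedom.
- Adjust for baseline score and, as far as about 14 schools allow, the randomisation strata (region and free school meal level). At school level the count alone leaves 14 − 2 = 12 degrees of freedom. Adding mean baseline score, region and free school meal stratum leaves 14 − 5 = 9, so there is little room for more.
- State that the result is an exploratory, non-randomised association and will not be presented as evidence that more components cause better outcomes.

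Both the model and the label are needed: the first corrects the error rate, and the second limits what may be concluded.

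The cost is a few lines of text and a model specification, with no new data. The downside is wider intervals and a weaker claim for a secondary hypothesis.

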### Methods in analysis to handle protocol non-adherence and any statistical methods to handle missing data {20c}

Missing data will be reported and associations between outcomes considered. A sensitivity analysis will be undertaken if deemed appropriate, depending on the extent of the missing data.

### Plans to give access to the full protocol, participant-level data and statistical code {31c}

As stated in the information sheets for headteachers and parents, no individual participant-level data will be available outside of the research team. The datasets analysed during the current study and statistical code are available from the corresponding author on reasonable request, as is the full protocol.

### Oversight and monitoring

#### Composition of the coordinating centre and trial steering committee {5d}

Once recruitment is underway, a Trial Steering Group will be set up comprising representation from the University of Leeds, Purely Nutrition Ltd., North Yorkshire County Council and Primary Schools in Harrogate or Selby. The Trial Steering Group will meet online, at a minimum, 4 times during the trial: an initial meeting to discuss the role of the group, 2 weeks before both data collection time points and at the end of the Trial for a close-out endpoint discussion and final feedback.

The coordinating centre Research Team at the University of Leeds will provide oversight of the whole trial design, day-to-day management of the trial, data management processes, analysis, report writing and decisions on publications. The coordinating centre research team will meet every 8 weeks throughout the trial to monitor the progress and data collection, consider risks and address any issues raised by the Trial Steering Group members.

#### Composition of the data monitoring committee, its role and reporting structure {21a}

The coordinating centre research team (KV, CE, JeC and MaH) will provide the function of data monitoring, including the oversight of the data management processes and quality control. This work will take place as part of the formal PhD supervision processes at the University of Leeds, the sponsor of the study. The lead researcher (KV) will report to the Trial Steering Group on data monitoring issues on behalf of the coordinating centre research team.

#### Adverse event reporting and harms {22}

Adverse events (for example, any minor mishaps or injuries that occur due to food preparation or food cooking activities) will be identified in discussion with Purely Nutrition Ltd., recorded in a secure place and reported in a timely fashion to the Steering Group.

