### Trial design {8}

The PhunkyFoods evaluation design is a parallel, cluster randomised controlled trial, with two arms and with a 1:1 allocation ratio. The intervention arm will receive the PhunkyFoods programme starting in May 2022, and the wait-list control arm will receive the PhunkyFoods programme after the final research data collection, with training from May 2023 (superiority trial). If the trial is not able to recruit 28 schools within the recruitment period, then the research team will consider an unequal allocation ratio with a smaller number of schools in the control group or widening the geographical recruitment area. The impact of this is discussed in the section on sample size.

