### Interventions

#### Explanation for the choice of comparators {6b}

The control group schools will receive their usual existing school curriculum for food science as delivered in the Food Technology schemes of work, without any support from the PhunkyFoods Programme. This may include specific nutritional components, designed and delivered by the school. In the UK, the Department for Public Health sets out the topics that should be covered in Food Technology lessons for primary schools [11] but in reality, this is likely to look different across school settings. We will ensure we collect relevant information on what schools are currently doing in relation to food knowledge and skills and include this information in the analysis as an additional independent variable if deemed appropriate.

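### The only stated route for identifying adverse events is discussion with the programme provider, which has no stated contact with control schools during follow-up

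*Protocol article*

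**What the plan says.** The harms plan is one sentence, under Adverse event reporting and harms {22}. It gives as its example "any minor mishaps or injuries that occur due to food preparation or food cooking activities" and says that such events "will be identified in discussion with Purely Nutrition Ltd., recorded in a secure place and reported in a timely fashion to the Steering Group". The example is not restricted to one arm, to a type of session leader or to a place.

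On the provider, Objectives {7} describes the programme as "developed and refined by Purely Nutrition". Strategies to improve adherence {11c} says that the provider runs it and that "All EDCs are employed by Purely Nutrition" (the EDCs are the delivery coordinators). The Steering Group has "representation from the University of Leeds, Purely Nutrition Ltd., North Yorkshire County Council" and also local primary schools ({5d}).

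On the control arm, {6b} says "The control group schools will receive their usual existing school curriculum for food science as delivered in the Food Technology schemes of work", and does so "without any support from the PhunkyFoods Programme". Trial design {8} adds that "the wait-list control arm will receive the PhunkyFoods programme after the final research data collection, with training from May 2023".

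**The concern.** How harms are found decides what can later be said about them. Here the one outside party named is the organisation whose programme is under test, and its stated work during follow-up lies in the intervention schools. Control schools also teach food technology, so minor injuries can happen there too, but nothing says how the trial would learn of them.

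The programme involves knife and cooking skills for children aged 7–9, so readers of the results will want a sentence on safety. If that sentence says that few or no events occurred, they need to know whether someone looked, and whether the same was done in both arms.

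**Working it through.** No arithmetic applies: the article gives no adverse event rate, threshold or expected count. The check is to set the harms sentence beside every section that could supply another source.

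1. **Provider's reach in the control arm.** {6b} rules out programme support for control schools, and {8} places their first programme contact after the last data collection, with training from May 2023. No provider contact with these schools is stated for the comparison period.

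2. **Provider's reach in the intervention arm.** Its coordinators work jointly with schools ({11a}), so some events in staff-led lessons or clubs could reach it. School staff are also trained to deliver content, and parents and children can use the online recipes (Abstract, Methods). No section asks staff or parents to report an event to the provider or to the researchers.

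3. **Routine data collection.** {18a} lists two child surveys completed in class and a fruit and vegetable diary completed at home, at T1 and T2. No harms item is mentioned.

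4. **Audit visits.** {23} provides for four visits, to intervention schools only, with dates arranged through the provider's representative on the Steering Group. The stated purposes are to observe activities, trial conduct and fidelity. Adverse events are not among them.

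5. **Oversight.** The research team meets every 8 weeks and considers risks ({5d}). The Steering Group meets at least four times: at the start, two weeks before each of the two data collections, and at close-out. These bodies can act on an event once it is known, but neither is given the task of finding one.

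6. **Independence.** The provider is developer ({7}), operator and employer of the coordinators ({11c}), named source of harms information ({22}) and a member of the receiving group ({5d}).

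Steps 1 to 5 leave one stated route, and it points to one arm. Step 6 shows that the route runs through a party with an interest in the result.

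**The case against.** The strongest reply is that the sentence says less than a critic may read into it. Events are to be identified in discussion with the provider, which makes the research team a party to the step; nothing calls the discussion exclusive. A reader might infer that the provider alone reports harms, but the text does not support that. The receiving group also includes the university, the county council and schools, so the provider does not control it.

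A reader might also infer that control-arm events cannot be counted at all, or that teacher-led and home cooking are excluded. The documents do not say so. The example of an adverse event is not limited by arm, leader or place; {6b} withholds programme support from control schools, not event recording; and coordinators may well hear of events in staff-led sessions. The supportable statement is that no route is stated. Nor can the gap be given a number. The share of events that the provider would see is not documented, and a simple upper bound on risk from zero events would treat children within a school as independent.

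It can further be said that the article is condensed, that a full protocol is available on request ({31c}), and that comparative harms are not a stated objective or outcome. All of this is true and keeps the point small. It does not remove it. Missing forms and timelines would be no finding, but the article does state an identification method, and that method can be judged as it stands.

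**Conclusion.** The point holds as a minor weakness in how harms are ascertained. If the published route is followed as written, harms information would come mainly from the intervention arm, with an interested party as the named source. A low or zero count would then be uninterpretable, and no comparison with usual practice could be defended.

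This rests on two assumptions: that the full protocol adds no route for control schools, school staff or parents, and that the audit visits and team meetings are not used for this purpose without saying so. If either fails, the gap narrows or closes, and the article's sentence only needs completing. The primary analysis, the secondary outcome and the sample size are unaffected.

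**What to change.** Amend {22} as follows:

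- Name the school contact in both arms as a source of adverse event information.
- At the T2 visit that already takes place, ask every school one identically worded question on injuries or reactions linked to food preparation since T1. Ask it after the child surveys, so that the answer cannot reveal allocation to an assessor who is blinded (blinding at T2 is planned but depends on funding, {17a}).
- Keep discussion with the provider as a supplementary route.
- Report counts by arm and by source. Base any between-arm statement only on the common school question, because the provider route adds detection in one arm alone.

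The cost is one question per school and one row in a table, with no extra visit or staff. The downside is recall over the 12 months from March 2022 to March 2023. That period crosses a school year, so the class teacher may have changed. Both limitations apply to the two arms alike.
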